### Harms

AEs will be documented from baseline (pre) until two weeks after the last follow-up (FU12), regardless of any causal relationship to the interventions. During the intervention period and for two weeks following each assessment visit, AEs and serious AEs (SAEs) will be documented in detail. During the remaining study period, only specific risk signals will be recorded: vertebral body fractures, increased osteoarthritis symptoms, activated osteoarthritis or arthritis of the lower extremity, general joint pain (which might indicate arthritis), muscle pain, increase in concerns about falling with impact on (instrumented) activities of daily living or participation in daily life, hospitalization, and mortality.

The severity of AEs is differentiated into grade 1 to 5: mild (grade 1), moderate (grade 2), severe (grade 3), life-threatening (grade 4), death (grade 5). If an (S)AE is assessed as grade 2 or higher, it will be reviewed and verified by medical staff.

All SAEs (grade > 2) during the follow-up period, and AEs (grade > 1) during the intervention period, as described above, will be reviewed and verified regarding causal relationship with the study and their severity classification by an independent data safety monitoring board (DSMB). The DSMB will discuss and decide on changes or discontinuation of the intervention based on the (S)AE reports.

All participants are covered by a subject and travelling accident insurance.

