### Statistical analysis

The primary outcome, the rate of unrecovered falls within 12 months after the end of the intervention period, will be compared between groups by a multi-level Poisson regression model with study center and randomization block as random effects, at a two-sided significance level of 5%. Analysis of the primary outcome will be done on the full analysis set according to the ITT principle, which will include all randomized participants analyzed in the group they were assigned to. Missing values will be replaced using multiple imputation by chained equations (MICE) with predictive mean matching as imputation method, assuming missing data are missing at random. In total, 10 datasets will be created based on the available data analyzed. Rubin’s rules [79] will be applied to pool results from each dataset. As a sensitivity analysis, a per-protocol analysis will be conducted, consisting of all participants without major protocol violations and with available data on the primary outcome. The intervention effect on secondary outcomes will be analyzed using the same approach as the primary outcome. Additionally, the effect of cognitive status on the primary outcome and key secondary outcomes (total falls, injurious falls, participants who fall, participants experiencing multiple falls, time to first fall, and falls per physical activity, dynamic reactive balance) will be investigated as subgroup analyses. The safety analysis will include calculation of frequencies and rates of (severe) adverse events (AEs) together with 95% confidence intervals on all randomized participants as treated. The analysis will be fully specified in a statistical analysis plan prior to database lock, and will be conducted using R and SAS/STAT^®^ software.

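### Seriousness and severity are mixed in the safety sections, so DSMB review of serious follow-up events depends on the severity grade that the DSMB is asked to verify

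*Protocol article*

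**What the plan says.** The Harms section of the protocol article states these rules:

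- **Recording.** "During the intervention period and for two weeks following each assessment visit, AEs and serious AEs (SAEs) will be documented in detail". In the remaining study period only listed risk signals are recorded; the list ends with "participation in daily life, hospitalization, and mortality".
- **Severity scale.** Grades run "mild (grade 1), moderate (grade 2), severe (grade 3), life-threatening (grade 4), death (grade 5". The article gives labels but no criteria for each grade.
- **Medical staff review.** "If an (S)AE is assessed as grade 2 or higher, it will be reviewed and verified by medical staff".
- **DSMB review.** "All SAEs (grade > 2) during the follow-up period, and AEs (grade > 1) during the intervention period" are reviewed and verified by the independent DSMB for causal relationship and for their severity classification.
- **Use by the DSMB.** "The DSMB will discuss and decide on changes or discontinuation of the intervention based on the (S)AE reports".

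The Statistical analysis section says that the safety analysis will include "calculation of frequencies and rates of (severe) adverse events (AEs"), with 95% confidence intervals, on all randomized participants as treated. It does not use the word serious.

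**The concern.** Seriousness and severity are different attributes of an event. Seriousness concerns what the event led to, such as hospitalization or death. Severity concerns its intensity on a graded scale. The article introduces SAE on the first axis, attaches a threshold from the second, and then uses the second axis alone in the analysis section.

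Two things are at stake. The first is oversight: the DSMB decides on changing or discontinuing the intervention, and the rule for what it reviews in follow-up leaves out serious events with a low grade. The second is clarity of counting: a reader cannot tell from the article whether the S in the bracketed abbreviation means serious or severe, and so cannot tell which events the safety analysis will set apart.

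**Working it through.** No sample size, power or event figure bears on this point, so there is nothing to recompute. The check sets the stated rules against each other by period and grade.

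**Step 1: which events the DSMB rule covers**

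| Grade | Intervention period, any AE | Follow-up, serious event |
|---|---|---|
| 1 mild | not sent | not sent |
| 2 moderate | sent | **not sent** (medical staff review only) |
| 3 severe | sent | sent |
| 4 life-threatening | sent | sent |
| 5 death | sent | sent |

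A grade 2 event in the intervention period goes to the DSMB even if it is not serious. A grade 2 event in follow-up does not go even if it is serious. A serious follow-up event at grade 1 gets neither medical staff review nor DSMB review.

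**Step 2: two readings of the bracket after SAEs**

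- *Definition:* an SAE is an event above grade 2. A serious event of grade 1 or 2 is then not an SAE. It is not sent, and it may not be counted as serious.
- *Filter:* SAEs are serious events, and those above grade 2 go to the DSMB. A serious event of grade 1 or 2 stays an SAE but is not sent.

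The gap in DSMB referral is the same under both readings. Only the counting consequence differs.

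**Step 3: which reading the text favours**

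- For a definition: the threshold starts exactly at the grade labelled severe, and the Statistical analysis section writes severe.
- For a filter: the same sentence has a parallel bracket for AEs above grade 1. That one cannot be a definition, because the scale also has mild AEs of grade 1. SAE is also expanded as serious.
- Neutral: the medical staff rule covers AEs or SAEs of grade 2 or higher. It is satisfied by grade 2 AEs together with SAEs of grade 3 or more, so it does not show whether an SAE can be grade 2.

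The filter is the more natural reading, but the text does not settle it.

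**Step 4: the verification task**

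The DSMB is to verify the severity classification. In follow-up it sees a serious event only if that event was already graded 3 or higher. It can correct an event graded too high. It cannot correct a serious event graded 2 that should have been 3, because that event is not sent. Around the threshold, verification works in one direction only.

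**Step 5: a boundary left open**

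Detailed recording applies in the intervention period and in the two weeks after each assessment visit. The DSMB rule then refers back to what was described above. It is unclear whether events in the windows after the six- and twelve-month visits fall under the intervention-period threshold or the follow-up threshold.

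**The case against.** The strongest reply is that this is loose wording around a deliberate triage. The threshold is lower during training, when harm from the intervention is most likely to show, and higher afterwards. Events are not lost: hospitalization is recorded in the remaining study period whatever its grade, and grade 2 events are reviewed by medical staff. The DSMB acts on the AE and SAE reports, a phrase not limited to events above grade 2. The article condenses a fuller protocol, which may hold seriousness criteria, grading criteria and the data fields. Most of this stands. It does not remove the stated limit on what the DSMB reviews, and medical staff review is not described as independent.

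A reader might infer several stronger things that the documents do not support:

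- *That serious events are equated with grade above 2, and that lower-graded ones are not counted as serious.* This needs the definition reading, and the parallel bracket for AEs speaks against it.
- *That a moderate hospitalization is missed by the DSMB.* This is plausible, but without criteria per grade the article does not show that a hospitalization can be graded 2.
- *That only severe events will be reported.* In the analysis section the word is in brackets, so all AEs are covered, and the detail is deferred to an SAP that is not shown.
- *That seriousness is not captured in the eCRF.* Nothing in the article shows this.
- *That a certain number of events escape review.* The article gives no hospitalization rate and no distribution of grades, so any count would rest wholly on assumed inputs, and zero is possible.

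**Conclusion.** The point holds as an inconsistency in a stated rule. The Harms and Statistical analysis sections use serious and severe interchangeably. On the wording, DSMB review of serious follow-up events leaves out two of the five grades, 1 and 2, under either reading of the bracket, and makes referral depend on the grade that the DSMB is meant to verify. Fatal, life-threatening and severe events are all referred, so the gap is confined to serious events judged mild or moderate.

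The conclusion assumes that the sentence on DSMB review is the operative referral rule and that the full protocol does not override it. The number of events affected is unknown. The possible loss of serious status is a risk of ambiguity only.

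The change should be made, and most follow-up was still ahead when the article was submitted. Recruitment began in November 2024 and submission was on 28 July 2025, less than nine months later, so no participant could have completed twelve months of follow-up. Of the planned 396 participants, 158 were enrolled, leaving 396 − 158 = 238 (238/396 = 60%) still to enter. The position after that date is not stated.

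**What to change.** Reconcile the Harms and Statistical analysis sections, and check the full protocol and SAP for the same wording:

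1. Use serious and severe as separate terms throughout, and state what the S in the bracketed abbreviation means in each section.
2. State whether the threshold after SAEs defines them or filters them.
3. Make DSMB referral of serious follow-up events independent of the severity grade that the DSMB is to verify. Leave the existing grade triggers for non-serious AEs unchanged.
4. State which referral rule applies in the two-week windows after the follow-up visits.
5. Report serious and severe events separately by arm in the safety analysis.

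If the full protocol already separates the two attributes, the change is one of wording only. Otherwise the cost is that wording plus a few more events for DSMB review. Nothing here alters treatment or sets a stopping rule.

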### Patient and public involvement

For ongoing consultation with the target population of the TRAIL study, a participatory research panel (https://uol.de/en/health-services-research/divisions/geriatrie/participatory-health-services-research) is available throughout the study, consisting of patients and healthcare stakeholders. This panel supports the research team during all phases of the study and provides input on the recruitment process, the development of information materials, and the practical implementation of the study. In addition, both the assessments and the intervention were pre-tested with volunteers from the target population to confirm that the study procedures were feasible and acceptable.

### Protocol amendments

The initial recruitment strategy focused on geriatric patients recruited from hospital and inpatient and outpatient rehabilitation settings. To expand the potential recruitment pool, the strategy was extended to the community setting. Additionally, the exclusion criterion for the TUG, used to screen for fall risk, was initially set at < 12 s. According to the recently proposed modifications to the Word Falls Guidelines algorithm for improved fall risk stratification [80], this criterion was revised to TUG < 10 s. These protocol amendments were approved by the local ethics committees at each study site and have also been documented in the trial registry (NCT06652828). Any future substantial amendments to the protocol will be submitted for approval to the ethics committees and documented in the trial registry.

## Discussion

The aim of the TRAIL study is to evaluate the efficacy of treadmill PBT to prevent unrecovered falls in fall-prone older adults with and without CI. To the best of our knowledge, this is the first multi-center randomized controlled trial specifically targeting a high-risk population for falls, with unrecovered falls as the primary outcome.

In previous studies on the efficacy of PBT for fall prevention, potential ceiling effects have been suggested, largely attributed to the inclusion of healthier, community-dwelling older adults with a lower risk of falling [30]. To address this limitation, older adults who complete the TUG in less than 10 s without the use of a walking aid will be excluded from this study [80], thereby ensuring a focus on individuals at higher risk of falls.

Importantly, individuals with moderate CI will be included in this study – a group that remains often underrepresented in fall prevention research [21]. To date, no study has specifically investigated whether PBT is equally effective and demonstrates similar retention in older adults with and without CI. The low training volume of treadmill PBT, which is expected to be sufficient to achieve a significant reduction in falls [24], may be particularly relevant for individuals with CI, for whom longer training periods are less likely to be accomplished. The treadmill PBT intervention was designed to closely resemble typical physiotherapy prescription practices within the German health care system, thereby facilitating its integration into routine care, if proven effective.

The sample size calculation was based on an anticipated 50% reduction in falls, informed by meta-analyses in older adults on reactive and volitional stepping interventions by Okubo et al. [75] and gait adaptability training by Nørgaard et al. [76]. PBT can be conceptualized as a specific form of gait adaptability training, as it challenges the ability to respond to sudden changes during walking. Therefore, the findings by Nørgaard et al. [76] were also considered relevant to the expected effect of the treadmill PBT intervention. This assumption has since been supported—though at a somewhat lower effect size—by a more recent meta-analysis by Devasahayam et al. [22], which reported a 39% reduction in alls through reactive balance training.

For fall reporting in older adults, prospective daily fall calendars with at least monthly reporting, followed by telephone calls to clarify missing data and gather additional details on falls and injuries, have been recommended [57]. Following the recommendations by Zieschang et al. [34] for fall reporting in older adults with CI, the TRAIL study will use a combined strategy of monthly returned daily fall calendars, regular once-monthly telephone calls, and proxy information to provide additional context or assess the plausibility of participant-reported falls in cases of missing, implausible, or contradictory information. The TRAIL study further extends these sources of information by encouraging participants and proxies to proactively report falls, which may enhance the completeness of fall data and support greater participant engagement in the reporting process.

PBT triggers automatic reflex-like balance responses that help to restore equilibrium without the need for conscious cognitive processing. This feature may be particularly beneficial for individuals with CI. In addition to its promising low volume, treadmill PBT is perceived as effective by both older adults and health care professionals [81, 82]. However, these positive perceptions must still be validated in populations with CI.

Reactive balance assessment will be conducted in both groups only at the 12-month follow-up, based on two considerations. First, such assessment could unintentionally influence reactive balance and fall outcomes in the control group, potentially confounding the effects of the PBT intervention. Second, exposing participants to their limits of reactive balance control already at baseline might cause anxiety about upcoming perturbations during the intervention period, which may lead to early dropouts [28]. However, given a successful randomization of participants, we assume a comparable level of reactive balance control in both groups at baseline. Therefore, if training effects are retained, differences in reactive balance may become evident at the 12-month follow-up.

The potential public health impact of treadmill PBT is considerable. The intervention could be implemented into existing health care structures such as day clinics, inpatient and outpatient physiotherapy settings, rehabilitation centers, or even fitness centers. Treadmill PBT offers a safe, task-specific approach to fall prevention, with a minimal risk of injury due to the use of a safety harness system. As such, it holds significant promise for improving care for the rapidly growing population of fall-prone older adults.

From an economic viewpoint, falls in older people pose a significant economic burden to society, accounting for 0.9% to 1.5% of total health care expenditures related to falls alone. In Germany, the costs for treating fall-related injuries exceeds 2 billion Euros, annually [83]. Treadmill PBT may be more cost-effective compared to conventional physical exercise. The minimal set up time of the perturbation treadmill (< 1 min) and the low training volume of treadmill PBT are important features for future implementation into health care systems and for broader scalability. However, the initial acquisition costs of the treadmill need to be considered, and the overall economic efficiency warrants further investigation.

## Conclusions

As one of the first treadmill PBT studies targeting a fall-prone older population, also including individuals with CI, the TRAIL study addresses key limitations of previous PBT research, which has predominantly involved healthier older adults. With only a limited training volume, treadmill PBT is expected to provide a high benefit for participants, including a meaningful reduction in falls in combination with functional improvements. Notably, these benefits may also extend to participants with CI – a population for whom effective fall prevention strategies are limited. Overall, the TRAIL study will provide important evidence on the clinical and public health value of treadmill PBT for fall prevention in a vulnerable population.

## Trial status

Recruitment for the TRAIL study started in November 2024. The current protocol version is 4.0, with the last amendment on March 25th, 2025. At the time of submission (28.07.2025), 158 participants have already been enrolled in the study.

## Data Availability

No datasets were generated or analysed during the current study.

## Abbreviations

2MWT: 2-minute walk test
AP: anterior-posterior
CALM: Compensatory Arm and Leg Movements
CI: cognitive impairment
COP: center of pressure
CSRT: Choice Stepping Reaction Time
CTT: conventional treadmill training
FU6: 6-month follow-up assessment
FU12: 12-month follow-up assessment
IMU: inertial measurement unit
ML: mediolateral
MMSE: Mini-Mental State Examination
MoCA: Montreal Cognitive Assessment
PBT: perturbation-based balance training
Post: post-training assessment
Pre: baseline assessment
ProFaNE: Prevention of Falls Network Europe
SPPB: Short Physical Performance Battery
STT: Stepping Threshold Test
TIDieR: Template for Intervention Description and Replication
TUG: Timed Up and Go
